### Statistical analysis

Efficacy and safety analyses will be conducted according to the intention-to-treat principle. All statistical analyses will be performed using Statistical Packages of Social Sciences software (SPSS; version 19.0). All results made in this study are based on two-sided tests. A *P* value < 0.05 will be considered statistically significant. Continuous data will be presented as means and standard deviations and compared using the independent *t* test or Wilcoxon’s rank sum test, while categorical data will be presented as percentages or frequencies and compared using the chi-square or Fisher’s exact test. Data for subjects who meet the dropout criteria (i.e., incidence of serious AEs, < 80% compliance with the protocol, incomplete data that could influence the trial, reluctance to continue the study, large error in protocol, or deviation from the protocol) will be excluded. Missing values will be implemented by multiple imputations.

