#### Intervention group

Patients in the treatment group will receive a 5-day Shenmai injection regimen plus conventional therapy. According to national guidelines, conventional therapy includes the routine use of antiemetic and gastro-protective agents. SMI will be manufactured by Huarun Ya’an Sanjiu Pharmaceutical Co., Ltd., based on good manufacturing practice (GMP) standards. Each milliliter of the injection is equivalent to 0.1 g of red ginseng (*Radix ginseng Rubra*) and 0.1 g dwarf lilyturf tuber (*Radix ophiopogonis*) of crude drug. It will be administered at a dose of 100 ml by intravenous infusion once daily for 5 days as a period. Treatment will be administered by Chinese medicine physicians with 5 years of formal university training in Chinese medicine, a license to administer treatment, and at least 1 year of clinical experience.

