Current evidence shows that SMI has a lower rate of ADRs. However, a systematic review of ADRs associated with SMI since 1995 showed that ADR cases were mainly systemic reactions (allergic shock), skin lesions (urticaria and pruritus), and local pain [43]. Because most ADRs occurred in the first 30 min of the first SMI administration, we suggest that patients should be closely observed during this period. Meanwhile, for patients who had continuous treatment with SMI, there is a need for close attention. ADR severity for each event as classified according to World Health Organization guidelines is shown in Table 1 [44].

**Table 1 Tab1:** Classification of adverse drug reaction (ADR) severity for Shenmai injection

Classification of ADR severity	
Class I	ADRs are deadly or life-threatening; patients need to be withdrawn from drugs and treated immediately; or ADRs last for more than 1 month.
Class II	Patients have pathologic and physiologic changes and must be withdrawn from drugs and treated; or ADRs last for more than 7 days.
Class III	Patients cannot endure the ADRs and must be given a lower dose or withdrawn from drugs; patients improve after symptomatic treatment.
Class IV	Patients can endure the ADRs, and no lowering of dose or drug withdrawal is necessary. Whether without treatment or through symptomatic treatment, patients improve

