### Sample size estimation

The primary endpoint is the fatigue severity self-assessed using the FACIT-F subscale. The sample size is calculated based on the primary endpoint. Previous clinical practice suggests a mean difference (MD) of 4.95 between groups, and the same standard deviation (SD) of 7.28 for each group. Using a superiority test, it is estimated that 38 participants per group are needed to achieve 90% power and a (two-sided) 5% significance level in detecting treatment differences. Thus, the final sample size has been set at a total of 94 patients (47 in each group), assuming a 20% dropout rate.

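### The plan defines no usable safety set: safety is placed under intention-to-treat, and the same paragraph then excludes patients with serious AEs, low compliance or early withdrawal

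*Protocol article*

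**What the plan says.** The Statistical analysis section of the protocol article sets one principle for both purposes: "Efficacy and safety analyses will be conducted according to the intention-to-treat principle". A few sentences later it lists dropout criteria that remove a patient's data. The list opens with "incidence of serious AEs, < 80% compliance with the protocol", goes on to incomplete data, and closes with "reluctance to continue the study, large error in protocol, or deviation from the protocol) will be excluded". Nothing limits that rule to efficacy, and the article names no separate safety set.

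Three other places bear on the point. SMI is given "by intravenous infusion once daily for 5 days as a period" (Intervention group), so full exposure is five infusions. The Safety section says that "most ADRs occurred in the first 30 min of the first SMI administration" and lists allergic shock among the reported reactions. Table 1 in that section grades reaction severity partly by whether the drug had to be withdrawn or, in Class III, its dose lowered.

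**The concern.** Safety is a stated aim, and the product is intravenous with known acute reactions. The reader needs to know how many patients who received SMI had a reaction, and how many of those reactions were serious. That takes a denominator of exposed patients and a numerator from which no event has been removed.

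The paragraph secures neither. Under pure intention-to-treat, a patient assigned to SMI who never receives an infusion counts as exposed, although that patient cannot have an SMI reaction. Under the exclusion rule, having a serious AE is itself a ground for leaving the analysis. The two faults have different causes, but both tend to make SMI look safer than it is. Because the text does not say which rule prevails, the safety population could be settled after the data are seen.

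**Working it through.** The article gives no reaction rate, no size for a safety set and no number never infused, so there is no safety figure of the plan's own to reproduce. Rates and counts marked as assumed below are illustrations.

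**Inputs from the article**
- 47 patients per group, 38 of them evaluable, with 20% dropout allowed (Sample size estimation). The allowance per group is 47 − 38 = 9.
- Five planned infusions (Intervention group).
- Exclusion for, among others, "incidence of serious AEs, < 80% compliance with the protocol" (Statistical analysis).

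**Reading A: intention-to-treat governs.** Let k be the number of SMI-assigned patients never infused and p the reaction rate among those infused. The reported rate is p × (47 − k)/47. With p assumed to be 10%:

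| k (assumed) | Infused | Reported rate |
|---|---|---|
| 2 | 45 | 10% × 45/47 = 9.6% |
| 5 | 42 | 10% × 42/47 = 8.9% |
| 9 (extreme) | 38 | 10% × 38/47 = 8.1% |

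If no reaction is seen, the upper limit of the exact two-sided 95% interval is 1 − 0.025^(1/n). It is 7.5% for 0/47, against 7.9% for 0/45 and 9.3% for 0/38.

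**Reading B: the exclusions govern.** A never-infused patient has 0 of 5 infusions, which is 0% compliance, and is excluded. The denominator becomes 47 − k and the dilution is zero.

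The numerator now suffers. Take all 47 SMI patients as infused and assume 5 have an AE, of which s are serious. Excluding the serious cases changes the AE rate from 5/47 to (5 − s)/(47 − s):

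| s (assumed) | AE rate, all treated | AE rate after exclusion | Serious AE rate, all treated | Serious AE rate after exclusion |
|---|---|---|---|---|
| 1 | 5/47 = 10.6% | 4/46 = 8.7% | 1/47 = 2.1% | 0 |
| 2 | 5/47 = 10.6% | 3/45 = 6.7% | 2/47 = 4.3% | 0 |
| 3 | 5/47 = 10.6% | 2/44 = 4.5% | 3/47 = 6.4% | 0 |

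The last column is zero by construction, whatever happens in the trial.

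Non-serious reactors can be lost as well. If compliance is measured by infusions given (the article does not define it), a patient who stops after one, two or three infusions has 1/5 = 20%, 2/5 = 40% or 3/5 = 60%. All three are below the 80% cut; four infusions, 4/5 = 80%, is not. As most reactions are said to come with the first infusion, a reaction that ends treatment will usually put the patient below the cut.

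**The case against.** A reader might infer from the intention-to-treat sentence alone that never-infused patients will enter the SMI denominator and that the reaction rate will be materially understated. The documents do not support that much, for four reasons.

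- The exclusion sentence, read as written, removes those patients, and a control patient given SMI would also be removed, as a protocol deviation. Dilution then does not arise.
- The 20% dropout allowance inflates the sample size for the fatigue endpoint and says nothing about when patients leave. Placing all 9 before the first infusion is an extreme. Participants are oncology inpatients who consent before randomisation and have a 5-day course, so few are likely to go uninfused. At k = 2 the shift from 10% to 9.6% would change no conclusion.
- The dilution formula assumes no events in uninfused patients. That suits SMI reactions, but not AEs at large: these patients are on chemotherapy, and the plan counts AEs whatever their cause.
- Causality is recorded for every AE, so a rate per infused patient could be produced from the data collected.

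All four stand, and they reduce dilution to the lesser half of the problem. They do not rescue the paragraph, because the rule that removes the dilution is the one that removes serious events.

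It would also go too far to say that the plan conceals serious AEs. They must go to the monitoring and ethics committees within 24 h, and all AEs are recorded on case report forms. The fault lies in the analysis set, not in capture or oversight.

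**Conclusion.** The point holds as a contradiction that leaves safety without a valid analysis set on either reading. The article states both rules, so this is not detail left to an analysis plan.

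Under intention-to-treat the bias is probably small: 10% reported as 9.6% with 2 never infused, and 8.1% only in the extreme case of 9. Under the exclusions it can be larger. In the example with 2 serious cases among 5, the AE rate drops from 10.6% to 6.7% and the serious AE rate from 4.3% to nothing. These sizes rest on an assumed 10% reaction rate, assumed numbers never infused and assumed event counts, since the article gives none of them. The direction does not depend on the exact values: unexposed patients in the denominator lower a reaction rate, and removing patients because they had a serious event lowers the event rate. The point should be corrected before the data are analysed.

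**What to change.** Reconcile the two sentences in the Statistical analysis section as follows.

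1. Limit the intention-to-treat statement to efficacy.
2. Define a safety set analysed by treatment received. The SMI group is every patient given at least one SMI infusion, including any control patient who received it. The control group is patients assigned to control who received no SMI.
3. List SMI-assigned patients who were never infused separately, with any AEs they had. Do not move them to control: those who left early would add little observed time and lower the control AE rate in turn, and they are a self-selected addition to a randomised group.
4. State that the dropout exclusions (serious AE, low compliance, withdrawal, deviation) do not apply to the safety set.

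The cost is a few lines of text and one analysis-set flag, with no new data collection. The downside is that the safety set may differ from the randomised groups by a few patients. Reporting the number moved or listed separately, by assigned group, keeps that visible.

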### Primary outcome

#### Fatigue severity

Fatigue severity will be self-assessed using the Functional Assessment for Chronic Illness Therapy-Fatigue (FACIT-F) subscale at baseline and on day 5. FACIT-F is a well-validated quality-of-life instrument widely used for the assessment of CRF in clinical trials. It consists of 27 general quality-of-life questions divided into four domains (physical, social, emotional, and functional) and the 13-item FACIT-F fatigue subscale [33]. FACIT-F allows patients to rate the intensity of their fatigue and its related symptoms on a scale of 0 to 4 (0, not at all; 4, very much). The total score for FACIT-F is the sum of the four domains (physical, social, emotional, and functional) plus the fatigue subscale.

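### The primary comparison ignores the baseline FACIT-F score and leaves both the test and the form of the endpoint open; one baseline-adjusted model should be named, with a power gain that depends on an unstated correlation.

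*Protocol article*

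**What the plan says.** Under Fatigue severity, the protocol article has the fatigue score self-assessed with the FACIT-F "subscale at baseline and on day 5". Sample size estimation confirms its role: "The primary endpoint is the fatigue severity self-assessed using the FACIT-F subscale". The planning values there are "Previous clinical practice suggests a mean difference (MD) of 4.95 between groups" and "the same standard deviation (SD) of 7.28 for each group", and the article does not say whether this SD belongs to the day-5 score or to the change from baseline. From them it concludes that "38 participants per group are needed to achieve 90% power and a (two-sided) 5% significance level in detecting treatment differences", and that "the final sample size has been set at a total of 94 patients (47 in each group), assuming a 20% dropout rate".

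Statistical analysis gives a single rule for all continuous outcomes: "Continuous data will be presented as means and standard deviations and compared using the independent" t test or the Wilcoxon rank sum test. It adds that "All results made in this study are based on two-sided tests". It names no baseline covariate, no rule for choosing between the two tests, and no statement of whether day-5 scores or changes are compared. No section gives a baseline to day-5 correlation.

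**The concern.** Two things are at stake.

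- **Precision.** Each patient is to supply a baseline value of the primary outcome, and the stated tests do not use it as a covariate. A test on day-5 scores leaves the variation explained by baseline in the error term. A test on changes subtracts the whole baseline score, which adds noise when the correlation is modest: with equal SDs at both times, the change is more variable than the day-5 score whenever r is below 0.5. A linear model with baseline as covariate estimates the weight from the data. This matters here because two-sided power at the planned evaluable number falls short of the stated 90%.
- **An open choice.** Two tests and two forms of the endpoint make four possible primary P values. If the choice were made after seeing results, the 5% level would not hold. The outcome is self-reported by patients who cannot be blinded, so there is good reason to close this freedom in advance.

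**Working it through.** **Inputs.** From Sample size estimation: difference 4.95, SD 7.28, two-sided 5%, 90% power, 38 evaluable and 47 randomised per group. The correlation r is an assumption and is varied.

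**1. The plan's own figure.** Normal approximation: n per group = 2 × (z_alpha + z_power)² × (SD/difference)², with (7.28/4.95)² = 2.163.
- Two-sided 5%: 2 × (1.960 + 1.282)² × 2.163 = 45.5, so 46. The exact t calculation gives 47.
- One-sided 5%: 2 × (1.645 + 1.282)² × 2.163 = 37.05, so 38.

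The stated 38 is therefore reproduced by a one-sided 5% test and not by the two-sided test in the text.

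**2. Power of the unadjusted two-sided t test.** Noncentrality = 4.95 / (7.28 × √(2/n)), with 2n − 2 degrees of freedom.
- n = 38: noncentrality 2.964, df 74, power **83.3%**. The Wilcoxon test under normality has about 81.6%.
- n = 47 (nobody lost or excluded): noncentrality 3.296, df 92, power **90.3%**.

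**3. ANCOVA at 38 per group if 7.28 is the day-5 SD.** Residual SD = 7.28 × √(1 − r²), df 73. At r = 0.3, for example, the factor is 0.954, the noncentrality 2.964/0.954 = 3.107 and the power 86.6%.

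| r | 0.1 | 0.2 | 0.3 | 0.4 | 0.5 | 0.6 | 0.7 |
|---|---|---|---|---|---|---|---|
| Power, % | 83.6 | 84.7 | 86.6 | 89.1 | 92.2 | 95.5 | 98.4 |

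90% is reached at r of about 0.43. The gap to 90% is 6.7 points, and r = 0.3 closes 3.3 of them, about half.

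**4. ANCOVA at 38 per group if 7.28 is the SD of the change.** With equal SDs at both times, the change SD is σ√(2(1 − r)) and the ANCOVA residual SD is σ√(1 − r²), so the residual SD = 7.28 × √((1 + r)/2).

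| r | 0.3 | 0.5 | 0.7 | 0.8 |
|---|---|---|---|---|
| Power, % | 95.2 | 92.2 | 88.7 | 86.9 |

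Here the gain shrinks as r grows, and power stays at or above 90% only up to r of about 0.63.

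Steps 3 and 4 assume normal outcomes and neglect the small loss from chance baseline imbalance.

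**5. Cost of the open choice, if made by result.** Simulation under no treatment effect, normal data, 38 per group, 20,000 trials per value of r, taking the smallest of the four P values: false-positive rate 10.3%, 10.5% and 11.3% at r = 0.3, 0.5 and 0.7. Choosing only between the two t tests (day-5 or change) gives 8.7% to 9.6%. Choosing only between t and Wilcoxon on the same outcome gives about 6%.

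**The case against.** The strongest reply is that nothing here is an error. Under randomisation the unadjusted t test is unbiased and holds its level; chance baseline imbalance is already reflected in its standard error, so what is lost is precision. It also matches the two-mean calculation used for the sample size. This stands: the point is about efficiency and specification, not validity.

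A reader might infer that adjustment would recover most or all of the missing power. The documents do not support that. They give no correlation, and the entry requirement of an ESAS fatigue score of at least 4 may narrow the baseline range and lower it. At r = 0.1 or 0.2 the gain is about 0.4 or 1.5 points on the day-5 reading, and on the change reading the dependence on r runs the other way.

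A reader might also infer that the trial is certain to miss its stated power. That presumes the planned 20% loss. Statistical analysis names intention to treat and multiple imputation but also excludes patients who meet the dropout criteria; with 47 per group analysed, the unadjusted test has 90.3%.

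Nor do the documents show an inflated type I error. Inflation arises only if the choice is made by result, and statisticians are to be unaware of allocation, which reduces that risk without removing it.

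Finally, the choice of test is often left to an analysis plan that is not shown here. But the article does more than stay silent: it states the comparison method, and the method it states uses no baseline covariate and offers two tests.

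**Conclusion.** The point holds in conditional form. The article collects baseline FACIT-F, states only unadjusted tests, and settles neither the test nor the form of the primary endpoint. Adjusting for baseline gives higher power than the unadjusted 83.3% at every correlation computed, on either reading of the SD: from 83.6% at r = 0.1 to 98.4% at r = 0.7 if 7.28 is the day-5 SD, and from 95.2% at r = 0.3 to 86.9% at r = 0.8 if it is the change SD. The recommendation therefore does not depend on resolving the SD; the size of the gain does, and it also rests on an assumed r. If all 47 per group are analysed the stated power is already met, and adjustment still helps (96.5% at r = 0.5 on the day-5 reading).

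This is a worthwhile improvement, not the correction of an invalid test.

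**What to change.** Before any analysis by treatment group, name one primary analysis: a linear model of the day-5 FACIT-F fatigue subscale score on treatment group with the baseline score as covariate, reporting the adjusted mean difference with its 95% confidence interval at the two-sided 5% level. Leave no optional covariate in this model, since that would reopen the choice it is meant to close. Use the same model for the continuous secondary outcomes that have a baseline value. Keep the t test or the Wilcoxon test as a sensitivity analysis, naming which one and on which form of the score.

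State whether 7.28 is the SD of the day-5 score or of the change.

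The cost is a change of wording and one degree of freedom. The model runs in the software already named and needs no extra patients, visits or data.

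This does not repair Sample size estimation, where 38 per group fits a one-sided 5% test while the text says two-sided. That must be corrected separately.

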## Abstract

**Background:**

Cancer-related fatigue (CRF) is the most common symptom in patients with advanced non-small cell lung cancer (NSCLC) undergoing treatment with chemotherapy. However, evidence upon which to base management strategies is scarce. Traditional Chinese Medicine (TCM) has been shown to be beneficial to patients with CRF. Chinese herbal injections should be administered under an evidence-based approach. This trial aims to assess the efficacy and safety of the addition of the Shenmai injection (SMI) to conventional therapy for CRF in NSCLC patients undergoing chemotherapy.

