In traditional Chinese medicine (TCM), *qi* usually refers to life energy, which manifests simultaneously on the physical and mental-spiritual levels [24]. The quintessence of TCM is syndrome differentiation and treatment. From the perspective of TCM, CRF is recognized as deficiency syndrome pattern, which is mainly caused by deficiency of *qi* and disharmony of *yin* and *yang* [25]. Many patients with CRF have symptoms of fatigue, listlessness, shortness of breath, and weak pulse after chemotherapy. These symptoms are similar to the syndrome of *qi* deficiency in TCM theory. According to TCM theory, this herbal prescription has been identified as an effective medication to tonify *qi* for reducing general weakness [23].

Ginsenosides, extracted from ginseng, and ophiopogonis, extracted from dwarf lilyturf tuber, are the principal constituents responsible for the pharmacological activities in SMI [26]. There are several studies on ginseng for the treatment of fatigue, and studies in mice have shown that ginseng can alleviate fatigue [27, 28]. One large study evaluating ginseng in combination with vitamins and minerals in 232 patients who had functional fatigue for over 10 years concluded that the ginseng formula improved fatigue symptom scores statistically significantly more than vitamin placebo [29]. An abstract presented at the 2003 meeting of the American Society of Clinical Oncology evaluated ginseng in people with cancer. It reported that ginseng significantly improved total and average fatigue levels, even though the sample size was quite small (*n* = 20) [30].

This study aims to assess the efficacy and safety of the addition of SMI to conventional therapy for advanced NSCLC patients undergoing chemotherapy. The primary hypothesis is that the SMI plus conventional therapy (here our treatment group) will experience less fatigue, as measured using Functional Assessment for Chronic Illness Therapy-Fatigue (FACIT-F) subscale scores, than conventional therapy alone (here our control group). Secondary objectives are to evaluate the efficacy of SMI on the following factors: symptom distress scores, depression, sleep disorders, quality of life (QOL), levels of inflammatory indicators, and adverse events (AEs).

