## Discussion

CFR is a common and unavoidable side effect of current forms of cancer treatment. It interferes with daily activities of cancer patients and affects various aspects of life, including physiological, social, and psychological well-being [45]. The National Comprehensive Cancer Network provides an evidence-based guideline that includes pharmacological and nonpharmacological interventions [46]. However, it does not include TCM, which relieves the symptoms of CRF effectively. The use of Chinese herbal injections for treatment of CRF should adopt an evidence-based approach.

This study has some limitations. First, due to the nature of the intervention, blinding is impossible. We will make every effort to ensure that outcome assessors, laboratory technicians, data managers, and statisticians are unaware of the treatment allocations. Another limitation is the 5-day treatment period which does not have a follow-up. While many studies use 1- or 2-week treatment periods in the clinical trial setting [47, 48], it would be appropriate in future studies to administer treatment for longer periods with long-term follow-up research since fatigue is a chronic symptom and, in most cases, affects patients for far longer than several weeks. This could make the results more convincing.

Considering that SMI originated and developed mainly from the traditional medicinal system in China, which considered the constitution or specific characteristics of health status in prescribing medication, the concurrent use of outcome measurements reflecting the perspective of traditional medicine will be of interest in future studies. In traditional medicine in China, SMI is not prescribed for everyone but for those with *qi*-deficiency syndrome, which is defined as a hypersensitive, easily fatigable state [49]. Although fatigue is one of the typical symptoms of this *qi*-deficiency syndrome, other factors that constitute the syndrome may also be considered in studying SMI.

Despite its limitations, we believe that this study has the potential to contribute to the development of an effective intervention to help relieve CRF. It will also establish feasibility and provide preliminary evidence on the efficacy and safety of SMI in advanced NSCLC patients with CRF. Based on the results of the study, future studies should employ more subjects, establish an appropriate control group, and include long-term administration and follow-up.

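### Safety is part of the aim, but the only between-arm inference planned for it is testing at P < 0.05 with no interval, which says little about harm at 47 per arm

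*Protocol article*

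**What the plan says.** The abstract puts safety in the aim ("This trial aims to assess the efficacy and safety of the addition of the Shenmai injection (SMI) to conventional therapy"), and the Background section repeats it ("This study aims to assess the efficacy and safety of the addition of SMI to conventional therapy"). The same Background paragraph states a hypothesis for fatigue only and places safety at the end of the secondary objectives: "levels of inflammatory indicators, and adverse events (AEs". The Discussion is modest about what will come out: the study should "provide preliminary evidence on the efficacy and safety of SMI in advanced NSCLC patients with CRF".

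The Statistical analysis section covers both halves of the aim: "Efficacy and safety analyses will be conducted according to the intention-to-treat principle". It then sets one inferential scheme: "All results made in this study are based on two-sided tests. A *P* value < 0.05 will be considered statistically significant". For categorical data, which include adverse events, "categorical data will be presented as percentages or frequencies and compared using the chi-square or Fisher’s exact test". Continuous data, which include laboratory values, are summarised by means and standard deviations and compared by t test or rank sum test. No confidence interval is mentioned for any safety quantity. The same section excludes the data of patients who meet its dropout criteria, and a serious adverse event is one of these.

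The Safety section describes the harms reported for SMI: "ADR cases were mainly systemic reactions (allergic shock), skin lesions (urticaria and pruritus), and local pain". It also provides for CTCAE grading, a four-class severity scale for adverse drug reactions (ADRs), recording of causality, and review by an independent committee. The sample size of 47 per group rests on the fatigue endpoint alone.

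**The concern.** For safety, the useful question is how much harm remains compatible with the data. A significance test answers a different one: whether the data are incompatible with no difference. In a trial sized for a continuous fatigue score the two answers can diverge widely, because a clinically important excess of events will often return P above 0.05.

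The mismatch is sharpest for the harms that the protocol itself singles out. A reaction attributed to SMI can occur only in patients who receive SMI. The control count for that category is zero by definition, so comparing it between arms tells the reader almost nothing about the rate in treated patients.

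At stake is what the trial can say about the safety half of its aim. With P values and percentages alone, the report would give no stated limit on the reaction rate, and a non-significant table could easily be read as reassurance.

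**Working it through.** **Inputs from the protocol.** 47 randomised per group and 38 evaluable per group after dropout (Sample size estimation); two-sided 5% level and the choice of tests (Statistical analysis). The protocol gives no adverse event rate, safety margin or safety power, so there is no safety figure to reproduce. All event rates below are assumptions. (The fatigue calculation behind the 38 does not reproduce at a two-sided 5% level: 2 × [7.28 × (1.960 + 1.282) / 4.95]² = 45.5, or 46 per group. That is a separate matter; nothing below depends on it.)

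**Step 1: how many events are needed for significance against zero.** With k events in one arm of 47 and none in the other, the two-sided Fisher P is 2 × C(47,k) / C(94,k).
- k = 4: P = 0.117.
- k = 5: 2 × 1,533,939 / 54,891,018 = 0.056.
- k = 6: 2 × 10,737,573 / 814,216,767 = 0.026.

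Five of 47 is 10.6%, and this is still not significant. The Newcombe 95% interval for 5/47 minus 0/47 runs from 1.0 to 22.6 percentage points, which tells the reader far more than P = 0.056.

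**Step 2: chance of missing a real excess at 47 per arm.** Power is the sum, over all pairs of counts (a, b) with a higher rate in the SMI arm and P < 0.05, of Bin(a; 47, p1) × Bin(b; 47, p0). The miss rate is 1 minus this sum.

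| Assumed SMI v control rate | Miss rate, Fisher | Miss rate, uncorrected chi-square |
|---|---|---|
| 25% v 10% | 1 − 0.374 = 63% | 1 − 0.503 = 50% |
| 45% v 30% | 1 − 0.250 = 75% | 1 − 0.319 = 68% |
| 5% v 0% | 1 − 0.029 = 97% | 1 − 0.207 = 79% |
| 10% v 0% | 1 − 0.329 = 67% | 1 − 0.704 = 30% |

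The last two rows apply only to a category in which controls cannot have events. Expected counts there are small, so Fisher would normally be the test used.

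**Step 3: laboratory values.** For an assumed shift of 0.5 SD, a two-sided t test has power 0.669 at 47 per arm and 0.576 at 38. The shift is missed 33% and 42% of the time.

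**Step 4: what an interval shows.** With zero events in n patients, the exact two-sided 95% upper limit is 1 − 0.025^(1/n).
- n = 47: 1 − 0.025^(1/47) = 0.0755, or 7.5%.
- n = 38: 1 − 0.025^(1/38) = 0.0925, or 9.3%.

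For events seen equally often in both arms, 5/47 v 5/47, Fisher P is 1.0, yet the Newcombe 95% interval for the difference runs from −13.4 to +13.4 points.

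**Step 5: the exclusion.** These limits hold only if the numerator and denominator include every treated patient. If patients with serious adverse events are removed, as the dropout rule in Statistical analysis would have it, the worst cases leave the numerator, and a limit such as 7.5% no longer describes the treated group.

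**The case against.** The strongest reply is that the protocol states nothing wrong. P < 0.05 is introduced as a general significance threshold, not as a safety criterion. A reader might infer that P ≥ 0.05 will count as evidence of safety, but no section says so, and that reading should not be attributed to the plan. Safety is also not a co-primary aim: adverse events are a secondary objective, the only hypothesis concerns fatigue, and only preliminary evidence is promised. Sizing on the primary endpoint is normal, low power for adverse events is common at this size, and a margin is not usually set for secondary safety data. All of this stands.

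A reader might also infer that controls cannot have allergic or skin events at all, so that every such comparison is against zero. The documents do not support that. All participants are on chemotherapy, and adverse events are recorded in both groups whatever their cause. The zero is definitional only for reactions attributed to SMI, and the protocol does not say that those will be tested between arms.

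Further, percentages or frequencies will be reported, and an exact limit can be worked out from a count and its denominator. CTCAE grading, the ADR classes and committee review mean that safety does not rest on P values alone. But these grade and monitor events; none of them quantifies the excess harm still compatible with the data.

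Finally, interval reporting is often left to an analysis plan, which is not shown. That would answer a protocol that was silent. This one is not: it names safety analyses and says that all results rest on two-sided tests.

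**Conclusion.** The point holds as a weakness in the chosen method, not as a false statement. The protocol names significance testing as its only between-arm inference for safety. At 47 per arm that method is weakly informative: 5/47 v 0/47 gives P = 0.056, and an assumed 25% v 10% is missed 50% to 63% of the time. For reactions attributed to SMI the between-arm test does not address the rate at all, whereas an exact interval does. The Fisher P values and the upper limits (7.5% for 0/47, 9.3% for 0/38) follow from the group sizes alone. The miss rates rest on assumed event rates and would change with others.

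**What to change.** In Statistical analysis, add for safety data:

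1. The SMI-arm incidence of ADRs, and separately of serious and of allergic reactions, each with an exact (Clopper-Pearson) 95% confidence interval.
2. Between-arm risk differences for adverse events and mean differences for laboratory values, each with a 95% confidence interval.
3. A statement that the safety conclusion will quote the upper limits (for example, that 0/47 still allows a rate of up to 7.5%) and will not rest on non-significance.
4. A statement that these summaries include every patient who received SMI, including those with serious adverse events, whatever the dropout rule says for other analyses. Without this, the limits would be falsely reassuring.

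No margin, extra patients, visits or data are needed, and the planned tests may stay beside the intervals. The cost is a few sentences of analysis text and a more modest safety statement.
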